### Relevant concomitant care permitted or prohibited during the trial {11d}

Both groups of patients will receive conventional treatment and care during the perioperative period. These treatments will include fasting and drinking before surgery, the use of glycerine enema and fluid replacement, the postoperative use of analgesics, intravenous analgesia pumps, and hemostatic drugs, if necessary. Pain therapy and prophylaxis will include muscle relaxants, local anesthetics, anti-inflammatory drugs, opioids, nonsteroidal medications, and other medications. During the postoperative period, the patient may receive intravenous or oral pain medication as needed. All previous and concomitant medications will be administered as per clinical routine and according to the patient’s needs and demands. All information regarding the use of analgesic drugs will be recorded. Both groups of patients will use the same dose of hemocoagulase for preventive hemostasis. Prior to the commencement of the study, all investigators will receive standardized training on trial content, treatment strategies, evaluation, and quality control. Interventions will be carried out in accordance with good clinical practice guidelines.

### Intervention description {11a}

#### Nonpressure dressing group

In the nonpressure dressing group, gauze will be placed on the operative wounds of the patient after complete hemostasis is achieved, and then, the dressing will be placed on the gauze with foam adhesive dressing to avoid the perineum area. The purpose of the small layer of gauze is to prevent the foam adhesive dressing from affecting the wound and reduce bias.

#### Pressure dressing group

In the pressure dressing group, an operator will compress the wound with three layers of gauze (AM 9 cm × 11 cm × 12 cm) in a “tower” shape after achieving complete hemostasis. First, one layer of gauze will be folded twice over the surgical wound. Second, it will be covered directly with two layers of gauze and two pieces of silk tape (45 cm × 2.5 cm, 3M China Co., Ltd.) in a “Y” shape to press the gauze firmly. The two pieces of silk tape will be fixed on both sides of the groin toward the middle of the back with moderate strength, avoiding the perineum during application.

### Ancillary and post-trial care {30}

All participants will return to usual care after dressing removal at postoperative 24 h. As part of our safety protocol, we will monitor patients’ surgical wound pain, micturition, skin damage, and active bleeding. Any participants with the above abnormal situations will be contacted by the site coordinator who will inform the doctor for timely treatment.

#### Discontinuations

If participants are unable or unwilling to complete the treatment, or the doctor’s assessment suggests that it is inappropriate to continue the study intervention due to a severe adverse event, we will consider them to be treatment dropouts.

### Outcome measures {12}

#### Primary outcome measures

There will be two primary outcomes. The incidence of urinary retention within 24 h will be one of these; typically, patients cannot urinate by themselves after using a hot compress or drug assistance and finally undergo retention catheterization.

#### Secondary outcome measures

Postoperative pain will be measured at rest with routine care at 6, 18, and 25 h by using a visual analog scale (VAS) after the surgical procedure. The scale will range from 0 to 10 points, with higher scores indicating more severe pain [21]: 0 = no pain, 1~3 = slight pain that can be tolerated, 4~6 = pain that can be tolerated but affects sleep, and 7~10 = unbearable pain that affects not only appetite but also sleep.The change in hemostatic effect scores within 25 h will be the other primary outcome. The effect of hemostasis will be graded using a 3-point ordinal scale: 0 = the dressing was not soaked before removal, 1 = there was no bleeding after changing the dressing due to excessive blood oozing, and 2 = postoperative bleeding requiring surgical revision occurred.The change in mean rectal tenesmus sensation scores within 25 h will be graded using a 3-point ordinal scale: 0 = no abnormal sensation; 1 = mild anal discomfort, occasionally abnormal sensation; 2 = strong foreign-body sensation; and 3 = strong foreign body sensation that is not easily relieved after rest or treatment.The incidence of medical adhesive-related skin injuries will be measured. The skin condition will be assessed by a senior wound specialist nurse. If there is no skin damage, “no” will be recorded. When any of the following situations occur, “yes” will be recorded: (1) exfoliation, (2) tension blisters, (3) skin lacerations, (4) contact dermatitis, and (5) allergic dermatitis. In the statistical analysis, the incidence of medical adhesive-related skin damage will be calculated by a statistician.The change in the mean anal edema score when the dressing is removed 24 h after surgery will be graded using a 4-point ordinal scale: 0 = no anal edema, 1 = mild edema (< 1/4 anal area ), 2 = moderate edema (1/4 to 1/2 anal area ), and 3 = severe edema (> 1/2 anal area ).The total dose of analgesics before removing the dressing will be recorded.The length of hospitalization will be recorded in days.Hospitalization expenses will be recorded.

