**Methods:**

In this study, we plan to include 186 patients who have undergone modified Milligan-Morgan hemorrhoidectomy, which only sutured external hemorrhoids to reduce the risk of bleeding. The purpose is to determine whether the use of nonpressure dressings after open hemorrhoidectomy is inferior to the use of pressure dressings in terms of severe postoperative bleeding and postoperative complications. The primary endpoints of the trial are the incidence of urinary retention within 24 h after surgery and the incidence of severe postoperative bleeding 1 h after dressing removal, which requires revision surgery within 24 h after the surgery. The secondary endpoints of the study are the pain score, anal distension score, postoperative use of analgesics, and incidence of medical adhesive-related skin injury, all of which will be assessed before removing the dressings. The length of hospitalization in days and hospitalization expenses will be recorded. Safety will be assessed with consideration of all adverse and severe adverse events related to the study treatment.

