## Randomization and blinding

Randomization will be performed by an independent statistician with no clinical involvement in this trial by use of a random number generator program in Excel software (Kingsoft Office Software Co. Ltd., China). A simple randomization method and table of random numbers will be used. If the selected number is even, the patient is allocated to the nonpressure dressings group, and if it is odd, the patient is allocated to the pressure dressings group in a 1:1 ratio. Only one data administrator can access the random number table on the computer. An independent staff member who will not take part in the performance of this study will seal the random numbers in opaque envelopes. Then, the primary investigator will save these envelopes and open one of them when a participant is enrolled.

The participants will be enrolled by nursing staff and research assistants in the order of admission time. And they will be grouped by the data administrator using the table of random numbers. The two groups will use different types of dressings, and the operators will place the dressings. The patients can feel whether the wound is pressurized, so they cannot be blinded. However, the operators will remove the dressing before the observer’s follow-up. The observers and statisticians will be blinded to the group assignments.

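### The three-level hemostatic score leaves bleeding controlled without surgery either ungraded or at the best grade, and two of its levels overlap

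*Protocol article*

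**What the plan says.** The section on secondary outcome measures in the protocol article fixes the score itself. The lowest level is "0 = the dressing was not soaked before removal". The other two are given as "there was no bleeding after changing the dressing due to excessive blood oozing, and 2 = postoperative bleeding requiring surgical revision occurred". The window is 25 h. The section on ancillary and post-trial care puts dressing removal at 24 h, so the last hour of the window is spent without the trial dressing. The statistical analysis section compares graded data with the Mann-Whitney U test.

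The status of the score is stated in conflicting ways. The outcome section says "The change in hemostatic effect scores within 25 h will be the other primary outcome". The objectives name urinary retention as the only primary objective and list the score among the secondary ones, and the sample size rests on retention alone. The abstract names a different bleeding endpoint as primary: "the incidence of severe postoperative bleeding 1 h after dressing removal, which requires revision surgery within 24 h after the surgery".

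Bleeding also appears outside the outcomes. Patients are monitored for "surgical wound pain, micturition, skin damage, and active bleeding", and anyone with such a problem "will be contacted by the site coordinator who will inform the doctor for timely treatment". Adverse events are graded by CTCAE v4.03 and compared by severity with Fisher's exact test. The only bleeding event named there is severe hemorrhage.

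**The concern.** An ordinal outcome works only if every patient belongs to exactly one level and a worse course never gets a better level. This score appears to fail on both counts, in the middle of the bleeding range.

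That range matters here. The background says that pressure is applied mainly to stop bleeding, and the discussion asks whether it can be left out routinely. The background also calls active bleeding in the first 24 h very rare, so bleeding that leads to re-operation should be rarer still. Most of what the trial can show about bleeding would then lie short of surgery, where the levels are badly drawn. An assessor who meets such a patient must improvise: leave the item blank, call it grade 1, or call it grade 2.

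This is not detail left to an unseen analysis plan. The protocol article states the level definitions, and grading happens at the bedside. An analysis plan could repair it later only if the course of the bleeding had been recorded somewhere else.

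**Working it through.** The plan gives no figure on this point, and the total of 186, which is sized on retention, does not enter. The check is an enumeration.

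**Inputs.** Level definitions and the 25 h window: secondary outcome measures. Removal at 24 h: ancillary and post-trial care. The endpoint that counts only revision surgery: abstract, methods.

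**Step 1. The possible courses.** The dressing is dry or soaked (2 states). What follows is no bleeding, bleeding controlled without surgery, or revision surgery (3 states). That makes 2 × 3 = 6 cases. I take a soaked dressing to be one that is changed for oozing, as grade 1 implies.

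**Step 2. Apply the stated levels literally.**

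| Dressing | What follows | Grade as written | Event under the abstract's endpoint |
|---|---|---|---|
| Dry | No bleeding | 0 | No |
| Dry | Bleeding after removal, controlled without surgery | 0 | No |
| Dry | Revision surgery | 0 and 2 | Yes |
| Soaked, changed | No bleeding | 1 | No |
| Soaked, changed | Bleeding continues, controlled without surgery | none | No |
| Soaked, changed | Revision surgery | 2 | Yes |

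The last column disregards the timing conditions in that endpoint.

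**Step 3. Read the result.** Three of the six cases get one sensible grade. One has no grade: grade 1 demands that bleeding has stopped, and grade 2 demands surgery. One gets the best grade despite bleeding, because grade 0 looks only at the dressing up to its removal while the window runs one hour longer (25 − 24 = 1 h). One fits two grades. Both non-surgical bleeding cases are non-events under the abstract's endpoint, so neither bleeding outcome shows them as bleeding.

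**Step 4. Test the replacement.** Use four levels, worst grade within 25 h: 0 = dressing unsoaked and no bleeding once it is off; 1 = changed for oozing, then no bleeding; 2 = bleeding after a change or after removal, controlled without surgery; 3 = revision surgery for bleeding. In the order of the table the six cases become 0, 2, 3, 1, 2, 3. Each case has exactly one grade, and within each dressing state the grade rises as the course gets worse.

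**The case against.** **Grade 1 can be read generously.** It may mean oozing that dressing changes settled, so that a patient who stops bleeding after a second change is grade 1. That is fair, and it narrows the ungraded case to bleeding stopped by some other non-surgical means. It does nothing for the dry dressing followed by bleeding, which the text puts at grade 0.

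**The overlap is harmless in practice.** Any sensible assessor would give a re-operated patient grade 2. Agreed, but the rule that the worst grade counts is nowhere stated.

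**Adverse event reporting catches this bleeding.** In part it does: active bleeding is monitored, a physician examines patients at each visit, and severity is compared by arm. The document does not reproduce the CTCAE grade definitions, so whether severity would separate these patients cannot be settled from it. Safety reporting also leaves the outcome itself misgraded.

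**Such patients are not foreseen.** The concomitant care section allows "the postoperative use of analgesics, intravenous analgesia pumps, and hemostatic drugs, if necessary", but this is a list of routine care and is not tied to active bleeding, so it is weak support. The monitoring provision is better evidence, because it expects active bleeding to be noticed and treated, though it does not say how.

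**Stronger readings.** A reader might infer that bleeding after a dry removal has no grade at all. It has one, the wrong one. A reader might infer that a primary endpoint is undermined. The outcome section does call the score primary, but the objectives make it secondary and the sample size ignores it. A reader might also want an added composite of rescue measures. The document does not support that: it describes no rescue compression, a switch to a pressure dressing could occur in only one arm, and the trigger would lie with staff who know the allocation ("The two groups will use different types of dressings, and the operators will place the dressings").

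**Conclusion.** The point holds as a defect of definition. One of six possible courses has no grade, one is graded as the best outcome despite bleeding, and one fits two grades. This rests on the literal wording and on removal at 24 h within a 25 h window, and on no assumed event rate.

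The number of patients affected cannot be derived. The document gives no rate of non-surgical bleeding, and its remark that active bleeding is very rare suggests few. No direction of bias between the arms can be claimed either. The urinary retention comparison is untouched. Whatever its disputed status, the score is the only graded bleeding measure among the efficacy outcomes, so it should classify correctly.

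**What to change.** Replace the three levels with four and state that the worst grade within 25 h is used:

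- 0: dressing unsoaked, and no bleeding once it is off
- 1: dressing changed for oozing, with no bleeding afterwards (say explicitly that a dressing first found soaked at the 24 h removal belongs here if nothing follows)
- 2: bleeding after a change or after removal, controlled without surgery
- 3: bleeding that led to revision surgery

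Report the number of patients at each level by arm beside the planned Mann-Whitney test. The gain is correct grading and a visible count of non-surgical bleeding. It should not be presented as a gain in power.

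The cost is one more level on the case report form and one sentence of analysis, with no extra patients or visits. The drawback to state is that the new intermediate grade depends partly on judgment by staff who know which dressing was used. No composite outcome is needed, and the other endpoints stay as they are.

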## Study organization

### Data collection and management {19}

The researchers will independently record demographic and clinical data for all patients. Preoperative data will be collected within 1 day after recruitment. Postoperative data will be collected within 2 days after surgery. The organizational structure of the trial is as follows. The steering committee will have full oversight over the design of the trial. The investigators of the Data Management Safety Committee (DMSC) will supervise and confirm that the case report form (CRF) is correctly completed and that the data are consistent with the original data. If there are any errors or omissions, the investigator will immediately correct them. We do not intend to collect personal information about potential or registered participants other than that typically collected during hospitalization. For confidentiality, the electronic health information will be encrypted in accordance with the hospital protocol. After the trial, personally identifiable information will be omitted and placed in a separate database for data analysis.

### Statistical analysis

The validity analysis of the study will be mainly based on intention-to-treat (ITT, all randomized cases) and per-protocol analyses (PP, cases that comply with the trial protocol, good compliance, and completed CRF). First, the Shapiro-Wilk test will be used to test whether the quantitative data follow a normal distribution. If the data are normally distributed, the mean value and standard deviation will be used to describe the quantitative data, and a *t* test will be used for analysis. Nonnormally distributed data will be expressed as the median and quaternary and compared using the Mann-Whitney *U* test. The qualitative data will be expressed as the frequency and percentage; non-grade data will be compared by the chi-square test, and grade data will be compared by the Mann-Whitney *U* test. Randomization will be performed 24 h prior to the surgical intervention. Data will not be collected and analyzed for patients not undergoing surgical intervention. If the scheduled surgery is not performed, the study participant will be excluded from the clinical trial. For every patient who is excluded from the trial after randomization and before the start of the observation period (postoperative wound with or without compression), another study participant will be included to achieve the number of cases needed. The randomization sequence will continue. The next patient will not necessarily be assigned to the same group as the excluded patient. This research will continue until the required number of evaluable patients is reached. Due to complications, a very small number of patients may not be able to comply with the randomly assigned treatment. The study will not exclude these patients. All statistical tests will be two-sided, and *P* < 0.05 will be considered statistically significant. If baseline factors are inconsistent between the two groups, subgroup analysis and multivariate analysis will be considered.

In the safety analysis, Fisher’s exact test will be used to compare the incidence of AEs and SAEs by category (severity) between the two groups.

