## Introduction

### Background and rationale {6a}

As people’s personal and work lifestyles change, the incidence of mixed hemorrhoids in China is increasing annually [1]. According to an epidemiological study, in 2016, the incidence of anorectal diseases among urban residents in China was 51.14%, and the incidence of mixed hemorrhoids was the highest among these diseases, accounting for 50.28% of all anorectal diseases [2]. In the USA, the incidence is approximately 4%, with the prevalence being highest between 45 and 65 years of age [3]. It is estimated that about 50% of Germans have symptomatic hemorrhoids, and some authors believe that up to 70% of people are affected by hemorrhoids [4]. Mixed hemorrhoids can occur at any age, and the symptoms include itching, pain, bleeding, swelling, prolapse of an anal tumor, foreign body sensation, etc. [5]. Although mixed hemorrhoids are not fatal or malignant, these symptoms can reduce a patient’s quality of life and have negative psychological and physical effects [6]. The treatment types include conservative treatment and surgical treatment. Mixed hemorrhoids with mild symptoms can be treated conservatively [7]. However, surgery is the initial treatment of choice in patients with symptomatic grade III–IV hemorrhoids [5, 6, 8]. Various surgical procedures have been used to treat symptomatic hemorrhoids in recent years, but (Milligan-Morgan) ligation is still considered the standard surgical procedure [9–13]. At the end of the operation, the wound is bandaged by a pressure dressing, which is the most traditional type of dressing that has been used clinically for many years [14]. The main purpose of pressure bandaging is to stop bleeding, but it may increase the incidence of postoperative complications, such as urinary retention, pain, anal swelling, and medical adhesive-related skin damage [12, 15–18]. Besides, clinical observation shows that with medical advances and the application of hemostatic drugs, the incidence of active bleeding within 24 h after modified Milligan-Morgan hemorrhoids surgery is very low. In addition, the necessity of pressure dressing after hemorrhoidectomy has received little scientific attention. A previous controlled trial included 67 patients who underwent Milligan-Morgan hemorrhoidectomy [19]. The data indicated that the use of a nonpressure dressing after hemorrhoidectomy reduces the incidence of urinary retention and catheterization. However, the incidence of severe postoperative bleeding and other postoperative complications was not assessed. There is no consensus on whether it is necessary and beneficial to use a nonpressure dressing after hemorrhoidectomy. The results of this randomized clinical study will preliminarily help answer this question.

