#### Secondary objectives

To assess the impact of pressure dressings versus nonpressure dressings surveillance on:
Pain score within 25 h after operation (6H\18H\25H);The change in hemostatic effect scores within 25 h after operation;The incidence of medically adhesive skin lesions;The anal edema score within 25 h after operation (6H\18H\25H);The anal dilatation score within 25 h after operation (6H\18H\25H);Dose of analgesics within 24 h after operation;Hospitalization costs; andLength of stay.

To assess safety, the incidence of adverse events (AEs) and severe adverse events (SAEs) between the two study groups will be compared to illustrate the potential risk to patients with nonpressure dressings after hemorrhoidectomy.

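### The normality-test rule would very probably reduce hospitalization cost to medians and a Mann-Whitney test, which do not estimate or test the difference in mean cost per patient

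*Protocol article*

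**What the plan says.** The Secondary objectives section sets out "To assess the impact of pressure dressings versus nonpressure dressings surveillance on" a list of outcomes that includes "Hospitalization costs". Under Secondary outcome measures the only statement on this item is "Hospitalization expenses will be recorded". No summary measure or separate analysis is given.

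The general rule in Statistical analysis therefore applies. It opens with a preliminary test: "First, the Shapiro-Wilk test will be used to test whether the quantitative data follow a normal distribution". For variables that pass this check, the plan keeps means: "If the data are normally distributed, the mean value and standard deviation will be used to describe the quantitative data", with a t test. Variables that fail it are handled differently: "Nonnormally distributed data will be expressed as the median and quaternary and compared using the Mann-Whitney" test. Tests are two-sided at 0.05.

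Two other statements bear on the cost distribution. The hemostasis scale foresees a costly event: "2 = postoperative bleeding requiring surgical revision occurred". The Background expects bleeding to be rare: "the incidence of active bleeding within 24 h after modified Milligan-Morgan hemorrhoids surgery is very low".

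**The concern.** The natural reading of a cost objective is how much more or less is spent per patient. That is the difference in mean cost; multiplied by the number of patients it gives the difference in total spending. A Mann-Whitney test asks instead whether patients in one arm tend to rank lower. A re-operated patient takes a top rank however large the bill, and a few such patients hardly move the median.

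The trial's own rationale describes a trade-off in which the two can part. The nonpressure dressing is hoped to spare a fairly common event (urinary retention with catheterization), and the feared harm is a rare, expensive one (revision surgery for bleeding). A cost statement built on ranks could favor the nonpressure dressing while mean spending is equal, or fail to show that mean spending is higher. The rule also lets a preliminary test decide whether the report is about means or medians, so the meaning of the cost result is not fixed in advance.

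**Working it through.** **Inputs from the protocol article.** 93 per arm, two-sided 0.05, and the switching rule above. The plan gives no cost figure to reproduce. Its only computed figure is the sample size for retention (44.7% vs 24.7%, 80% power). The unpooled formula gives (1.960 + 0.842)² × (0.447×0.553 + 0.247×0.753) / 0.20² ≈ 85 per arm, and 85/0.9 gives 95, or 190 in total against the stated 186. That is close enough, and only the 93 per arm is used below.

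**Assumptions (not in the documents).** Base cost is lognormal with mean 1 and CV 10-50%. A fraction p of nonpressure patients, and none in the other arm, is re-operated at an extra cost m times the mean. A saving of p×m makes the true means equal. Shapiro-Wilk is applied in each arm.

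**Step 1: how often the rule switches.** With lognormal costs and 2-10% re-operated, it goes to Mann-Whitney in 89-100% of simulated trials. With a normal base cost plus re-operations it does so in 81-100% at CV 10-20%, but in only 15-91% at CV 50%.

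**Step 2: a hand check, uniform saving.** Take p = 3%, m = 1.5, CV 15%. Every nonpressure patient saves 0.03 × 1.5 = 4.5%.
- Log-scale SD: √ln(1 + 0.15²) = 0.149. Shift: −ln(1 − 0.045) = 0.046.
- For a patient not re-operated, P(nonpressure costs less) = Φ(0.046 / (0.149×√2)) = Φ(0.218) = 0.586.
- Re-operated patients rank at the top: P(nonpressure costs more) = 0.97×0.414 + 0.03×1 = 0.431, which is 0.069 below 0.5.
- Null standard error: √(187 / (12×93²)) = 0.0424. The ratio is about 1.62, so the rejection probability is about Φ(1.62 − 1.96) = 37%.

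The 3% who are re-operated enter only as 0.03×1. Doubling their bill would change nothing in the rank statistic.

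**Step 3: simulation with equal true means, 93 per arm.** Rejection by the plan's rule:

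| Saving | Re-operated, extra cost | CV 10% | 15% | 20% | 30% | 50% |
|---|---|---|---|---|---|---|
| Every patient | 3%, 1.5× | 74% | 37% | 20% | 9% | 5% |
| Every patient | 5%, 1.5× | 99% | 75% | 44% | 19% | 7% |

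With 1% re-operated at 1× the rate is 4-8% across CV 10-50%. Welch's test on equal-mean data rejects in about 4-8%.

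**Step 4: saving through catheterization only.** Catheterization is paid for by 44.7% of pressure and 24.7% of nonpressure patients. This follows the Background rationale; the Sample size section prints the two rates the other way round. Equal means then require one catheterization to cost 0.03×1.5/0.20 = 22.5% of an average admission, or 0.05×1.5/0.20 = 37.5% with 5% re-operated. At CV 15% the rule now rejects in about 25-31%. At CV 10% with 3% re-operated it rejects in 40%.

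**Step 5: cheap catheterization.** If it costs 1-2% of an admission, with 3% re-operated at 1.5×, nonpressure is truly dearer by 4.5% − 0.20×(1 to 2%) = 4.1-4.3%. At CV 10-20% the rule rejects with a lower nonpressure median in only 1-2% of trials. At 5% of an admission the figure is 2-5% (CV 10-15%). Welch rejects in 11-21% in these scenarios, so here the rank test loses power and does not produce a false saving.

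**The case against.** The strongest reply is that the size of the problem is assumed. The documents give no cost level, spread, catheterization price or re-operation rate. Bleeding is called very rare, both arms receive the same preventive hemostatic drug, and severe hemorrhage is listed as a known event under both dressings, so re-operation in one arm only is not supported. The highest rejection rates also need a saving in every nonpressure patient. That could come from dressing materials, but no prices are given. All of this stands: no single error rate can be attached to this trial.

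A reader might infer that the nonpressure dressing will be declared cheaper at equal mean cost. The documents do not support that. It can happen, and under several plausible settings it happens no more often than chance.

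It can also be said that the protocol never names mean cost as its target, has no cost-effectiveness aim, and refers to a statistical analysis plan, not shown, which may settle the matter. That is why this is a minor point. But the protocol does not leave the analysis open. It states a rule that covers cost, and nothing shown exempts it.

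Finally, bleeding that needs revision is graded in its own right and adverse events are compared separately, so the harm itself is not hidden. That is correct, but it does not repair the cost comparison.

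**Conclusion.** The point holds in a limited form. The rule governs hospitalization cost, and for right-skewed costs at 93 per arm it will very probably leave medians and a rank p-value. Those do not estimate or test the difference in mean cost per patient. With equal means, the chance of a significant result runs from about nominal (rare re-operation, or CV near 50%) to roughly 25-75% at CV 15% with 3-5% re-operated at 1.5 times mean cost. The lower end applies if the saving comes only through catheterization, the upper end if it is uniform.

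These figures show that the mismatch can matter; they are not predictions for this trial. Skewness of cost is itself an expectation, not something the documents state. Even where the error rate is nominal, the report would lack a mean difference and its interval. Cost is secondary and the primary result is untouched, so this is a desirable improvement, not a serious flaw.

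**What to change.** In Statistical analysis, add one sentence that exempts hospitalization expenses from the Shapiro-Wilk switch. Report mean cost per arm and the difference in means with a bootstrap or Welch 95% confidence interval, whatever the normality test shows. State that expenses include catheterization and revision surgery. Give medians and quartiles as description only.

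This needs no new data. The price is a wider interval, driven by the few expensive patients, and low power: in the cheap-catheterization scenarios above, Welch's test detected the truly higher cost in only 11-21% of trials. The interval would at least show that uncertainty.
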